## Abstract

**Background:** Vaccine hesitancy (VH) is a significant public health challenge, especially during the COVID-19 pandemic. Despite extensive research on the psychological and socio-political determinants of VH, its psychophysiological mechanisms remain unexplored. Grounded in the Somatic Marker Hypothesis, this study aims to investigate the neurophysiological and affective processes underlying VH. **Methods:** Two experiments will assess sensorimotor resonance and affective processes in VH. In the first experiment, motor-evoked potentials (MEPs) will be recorded from the deltoid and extensor carpi radialis muscles while participants view images of people receiving COVID-19 and influenza vaccines, as well as blood injections (Block 1), and images of vial containing the same substances (Block 2). Facial electromyographic (EMG) activity will measure disgust and fear responses. In the second experiment, skin conductance response (SCR) will be recorded during a virtual reality-based fear conditioning and extinction paradigm. **Expected Outcomes:** We hypothesize that vaccine-hesitant individuals will exhibit altered sensorimotor resonance, higher affective responses to vaccination stimuli, and impaired fear extinction learning. Psychological traits such as disgust sensitivity, paranoia, anxiety, and dogmatism are expected to be associated with VH. **Conclusions:** By identifying the psychophysiological mechanisms of VH, this study will contribute to developing effective vaccine promotion strategies to address future public health emergencies.

## 1. Introduction

The COVID-19 pandemic has caused a profound transformation in the global healthcare landscape, resulting in over 5.6 million deaths [1]. It has also disrupted social and economic activities worldwide, affecting people’s mental health [2,3]. In response to the rapid spread of the virus, the global community prioritized the development of effective safety measures, with vaccines emerging as a central strategy to control the pandemic [4]. However, despite the availability of COVID-19 vaccines, vaccine hesitancy (VH)—defined as delay or refusal to accept the vaccine—has become a significant global challenge during COVID-19 pandemic [5,6]. The World Health Organization (WHO) identified VH as one of the top public health threats, with estimates suggesting that approximately 26% of the population exhibited resistance to the COVID-19 vaccination [7,8]. A comprehensive approach to addressing VH requires integrating demographic, social, environmental and psychological dimensions [7,9,10,11,12]. Examining these factors is important to combat hesitancy toward the COVID-19 vaccine, guide targeted interventions that sustain effective public health responses, and contribute to managing future pandemics [13]. For example, a systematic review of 23 studies identified key demographic and socioeconomic features influencing COVID-19 vaccine uptake [14]. Older age, higher income, and greater educational level were associated with higher vaccine acceptance [6,15]. Concerns about vaccine safety, distrust in pharmaceutical companies and governmental health policies, absence of prior influenza vaccination, and exposure to misinformation have been strongly linked to VH [6,16,17]. Moreover, religiosity has been associated with lower vaccine intent, particularly in communities were vaccine acceptance conflicts with cultural or religious beliefs [18]. From a psychological perspective, a large body of evidence has reported that individuals with paranoid tendencies, impulsivity, low conscientiousness or emotional instability exhibit greater VH [7,9,19]. Furthermore, dogmatic thinking patterns and reduced empathic capacity are correlated with increased reluctance toward vaccination [19,20,21]. Complementing these findings, a multinational study across 24 countries identified disgust sensitivity and anxiety toward medical procedures (e.g., injections) as critical psychological drivers of anti-vaccine attitude, alongside adherence to individualistic/hierarchical worldviews [9]. Notably, contextual factors such as needle phobia—prevalent in approximately 10% of the population—and maladaptive fear regulation mechanisms may further entrench avoidance behaviors, exacerbating VH [22]. Beyond psychological and contextual variables, political ideology has emerged as a debated determinant of vaccine attitudes. However, empirical evidence remains inconsistent: while some studies report a correlation between a conservative political orientation and increased VH [23], others find no statistically significant relationship [24].

Despite progress in understanding VH, the psychophysiological mechanisms underlying resistance, in the context of COVID-19, remain largely unexplored. Grounded in the Somatic Marker Hypothesis [25], which posits that bodily states and emotional responses shape decision-making, this study’s goals are as follows:Investigate sensorimotor mapping and affective-autonomic responses in vaccine-hesitant and accepting individuals, assessing emotional and physiological reactions to vaccination-related and unrelated stimuli. We will measure motor evoked potentials (MEPs) from the deltoid muscle—a relevant muscle for vaccine inoculation—and the extensor carpi radialis as a control muscle. Additionally, facial electromyography (EMG) will be recorded to assess fear and disgust responses, providing physiological markers of affective processing in response to these stimuli.Examine affective learning processes in VH through a Pavlovian fear conditioning and extinction paradigm, testing whether hesitant individuals exhibit altered fear acquisition, extinction patterns compared to non-hesitant controls. Importantly, no explicit information about vaccination will be provided during the task, allowing us to probe whether differences in basic fear learning mechanisms—independent of vaccine-related content—might underlie or predict vaccine hesitancy. This approach aimed to identify whether disruptions at any stage of the conditioning process are associated with negative attitudes toward vaccination. Skin conductance response (SCR) will serve as the primary psychophysiological marker of conditioned fear responses.Analyze demographic and psychological characteristics associated with VH by comparing experimental and control group on disgust sensitivity, paranoia, anxiety, empathy, intelligence, personality traits, political orientation, and dogmatism, using validated questionnaires.

## 2. Methods and Analysis

### 2.1. Experiment 1

#### 2.1.1. Participants

A total of 40 healthy participants, aged 18 to 50 years, will be recruited for a randomized-controlled study and categorized based on their attitudes toward COVID-19 vaccination:Vaccine-Hesitant/Resistant Group (*n* = 20): Individuals reluctant to receive the COVID-19 vaccine, identified using validated psychometric tools, including the Vaccine Hesitancy Scale [26] and the Vaccine Hesitancy Scale for COVID-19 Vaccination [27].Vaccine-Accepting Group (*n* = 20): Individuals who are vaccinated or express no hesitation toward vaccination. They will serve as controls.

Recruitment will be conducted through online advertisements and university mailing lists. To ensure comparability, groups will be matched by demographic variables, including age, gender, and educational level.

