### 2.7. Interventions

#### 2.7.1. Experiment 1

Prior to the experimental session, participants will complete demographic and psychological questionnaires. Following screening, the optimal scalp positions (OSP) and resting motor threshold (rMT) for the target (deltoid) and control (extensor carpi radialis) muscles will be determined. Participants will be seated 80 cm from a computer screen in a dimly lit room. The experimental visual stimuli will consist of pictures depicting scenes of vials and ongoing injections referring to blood sampling, COVID-19 vaccine, and influenza vaccine subtending a 10.5 × 5.8 cm region plus a neutral control stimulus consisting of a scrambled picture of the same dimension and form (see Figure 2).

For each type of stimulus in both blocks, 20 MEPs will be recorded. To ensure a balanced and unbiased presentation, stimuli will be randomly presented. A total of 16 MEPs per muscle and condition will be obtained and stored for offline analysis.

During stimulus presentation, TMS pulses will be delivered at 120% of rMT at randomized intervals (1100–1400 ms post-stimulus onset) to mitigate priming effects. EMG will record muscle activity from the levator labii superioris, which is associated with disgust responses, and the corrugator supercilii, linked to fear responses. Additionally, following the TMS session, participants will be presented again with the same set of pictures and will ask to rate their emotional responses using a 7-point Likert scale, where 1 indicated no emotional reaction and 7 indicated a very strong emotional reaction. Specifically, they were asked to evaluate the extent to which each image elicited feelings of alarm, disgust, fear, and anger.

#### 2.7.2. Experiment 2

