### 2.8. Statistical Methods

All statistical analyses will be conducted using Jamovi (version 2.6.23), an open-source statistical software based on the R 4.5.0 framework. A significant threshold of *p* < 0.05 will be applied to all analyses. Parametric methods will be employed under the assumptions of normality and homogeneity of variance, verified by Shapiro-Wilk or Kolmogorov-Smirnov and Levene’s tests, respectively. Non-parametric tests will be used if assumptions are violated.

#### 2.8.1. Experiment 1

A 2 × 2 × 3 mixed-design ANOVA will be conducted to analyze differences in MEP amplitudes, with group (Vax vs. No-Vax) as a between-subjects factor, muscle (deltoid vs. extensor carpi radialis), condition (Blood, COVID-19, influenza), as within-subjects factors.

EMG activity from the levator labii superioris (disgust) and corrugator supercilii (fear) will be analyzed using a 2 × 2 × 3 mixed-design ANOVA, incorporating group (Vax vs. No-Vax), muscles (levator labii superioris, corrugator supercilii), condition (Blood, COVID-19, influenza).

Significant interactions (*p* < 0.05) will be followed by Tukey’s HSD post hoc tests to identify condition-specific effects.

#### 2.8.2. Experiment 2

Habituation, fear acquisition, extinction, and recall will be assessed through Skin Conductance Response (SCR) amplitudes using a 2 × 2 × 3 mixed-design ANOVA. The analysis will compare responses to stimuli (CS+ threat-associated stimulus, CS− safety-associated stimulus) as a within-subjects factor, across groups (Vax vs. No-Vax) as a between-subjects factor and phases (habituation, fear acquisition, fear extinction) as a within-subjects factor. Similarly, subjective fear/disgust ratings (Likert scale) will be analyzed using a 2 × 2 × 3 mixed-design ANOVA, with group (Vax vs. No-Vax) as a between-subjects factor, and stimulus Type (CS+ vs. CS−) and phase (habituation, fear acquisition, fear extinction) as within-subjects factors. Significant interactions (*p* < 0.05) will be followed by Tukey’s HSD post hoc tests to identify condition-specific effects.

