## 3. Discussion

This study aims to provide novel insights into the psychophysiological correlates of vaccine hesitancy (VH). Grounded in the Somatic Marker Hypothesis [25], we hypothesize that bodily and emotional responses will play a crucial role in shaping vaccination attitudes. By investigating sensorimotor mapping, affective learning processes, and psychological predictors of VH, we seek to contribute to a more comprehensive understanding of this phenomenon.

### 3.1. Experiment 1

We predict significant differences in motor evoked potentials (MEPs) between vaccine-hesitant and vaccine-accepting individuals when exposed to COVID-19 vaccination imagery. Specifically, hesitant individuals may exhibit reduced MEP amplitudes in the deltoid muscle—a key muscle involved in vaccine administration—suggesting altered sensorimotor resonance in response to vaccination stimuli. This would align with previous research on embodiment, which posits that motor responses are modulated by observed actions [48,49]. The sensorimotor resonance may serve as a proxy for embodied affective states such as disgust or fear—emotions that are central to the Somatic Marker Hypothesis, which emphasizes the role of visceral and emotional signals in guiding behavior and cognition [25]. Therefore, a decrease in MEP amplitude may indicate a disruption of somatic marker signals, given that corticospinal excitability is sensitive to modulation by negative emotional states. This interpretation is supported by prior work demonstrating the influence of emotions—particularly aversive or defensive states on motor system activity [39,40,41,50,51,52,53]. We suggest that motor resonance changes, in this context, may index the embodied affective experience central to the SMH, thereby linking motor excitability to emotional and interoceptive processing.

Additionally, we anticipate increased facial electromyography (EMG) activity in the levator labii superioris and corrugator supercilii muscles in vaccine-hesitant individuals, reflecting higher levels of disgust and fear responses. If confirmed, these results would support the hypothesis that VH is influenced by affective biases linked to disgust sensitivity and anxiety [9,21].

### 3.2. Experiment 2

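### The planned omnibus ANOVA with Tukey follow-up cannot separate a COVID-19-specific MEP effect from a general vaccine effect; two named group contrasts would

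*Protocol article*

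**What the plan says.** All references are to the protocol article.

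- **Grouping (2.1.1).** Participants are "categorized based on their attitudes toward COVID-19 vaccination". The hesitant group is then "identified using validated psychometric tools, including the Vaccine Hesitancy Scale [26] and the Vaccine Hesitancy Scale for COVID-19 Vaccination [27", so one of the two named scales is not tied to COVID-19. Controls are "Individuals who are vaccinated or express no hesitation toward vaccination", with no vaccine named.
- **Link to influenza (1. Introduction).** Among the correlates of hesitancy, "absence of prior influenza vaccination, and exposure to misinformation have been strongly linked to VH".
- **Prediction (3.1).** "We predict significant differences in motor evoked potentials (MEPs) between vaccine-hesitant and vaccine-accepting individuals when exposed to COVID-19 vaccination imagery"; the expected direction is a smaller deltoid MEP in hesitant people. The Abstract states its affective hypothesis for vaccination stimuli in general.
- **Analysis (2.8.1).** The MEP ANOVA has group between subjects and "muscle (deltoid vs. extensor carpi radialis), condition (Blood, COVID-19, influenza), as within-subjects factors". Significant interactions go to Tukey's HSD, which is meant to locate the effects specific to a condition. No contrast of COVID-19 with influenza, or of vaccines with Blood, is named.
- **Control picture (2.7.1).** The stimuli include three picture types "plus a neutral control stimulus consisting of a scrambled picture of the same dimension and form". The scrambled picture is not a level of the condition factor.

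**The concern.** The Introduction gives a reason to expect that people hesitant about the COVID-19 vaccine will often react to influenza vaccination as well. Two explanations of a positive result are then open: a reaction to the COVID-19 vaccine, or a reaction to vaccines in general. They have different consequences for vaccine promotion, which is the use the article foresees for its results.

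The design can tell them apart, because it has a second vaccine and a non-vaccine needle procedure in the same factor. The analysis as fixed does not use that. If the omnibus interaction is significant and Tukey then flags the groups at COVID-19 but not at influenza, the authors would probably report a COVID-19-specific effect. Significance at one level and not at another is not a test that the two levels differ.

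**Working it through.** **Inputs.** From the protocol: 20 per group (2.1.1), r = 0.5 among repeated measurements and sphericity (2.1.2), two-sided α = 0.05 (2.8). Assumed, because the document does not give them: a deltoid group difference of 0.8 SD at COVID-19, none at Blood, and a share q of the COVID-19 difference at influenza, with q from 0 (purely COVID-19) to 1 (general vaccine effect). The group differences for (Blood, COVID-19, influenza) are therefore 0.8 × (0, 1, q). The plan has no figure of its own on this point.

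**1. Omnibus group × condition test, deltoid, 2 and 76 df.** The noncentrality is λ = (n/2) × SS/(1 − r), where SS is the sum of squared deviations of the three differences from their mean: SS = 0.64 × (2/3) × (1 − q + q²).

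- q = 0: SS = 0.427, λ = 10 × 0.427/0.5 = 8.53, power 73%.
- q = 0.5: SS = 0.320, λ = 6.40, power 60%.
- q = 1: SS = 0.427, λ = 8.53, power 73%.

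The term 1 − q + q² is the same at q and at 1 − q. The test is thus exactly as likely to be significant under a purely COVID-19 effect as under a purely general one, and a significant result does not favour either.

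**2. What Tukey compares.** The three-way table has 2 × 2 × 3 = 12 cells and 12 × 11/2 = 66 pairwise differences of means. Each is hesitant v accepting at one picture type, or one picture type v another within a group, or a mixture. The quantity that defines specificity is a difference of differences, and it is none of the 66:

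(COVID-19 − influenza) in hesitant − (COVID-19 − influenza) in accepting.

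Tukey is also costly for the comparison that the article does predict. The noncentrality for the group difference at COVID-19 is 0.8/√(2/20) = 2.53. The unadjusted t test on 38 df has 69% power. The Tukey critical value for 12 means on 38 df, divided by √2, is 3.48, and power falls to about 19%.

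**3. Two 1-df group contrasts, noncentral t, 38 df.** The within-person contrast SD is √(2 × 0.5) = 1 for a difference of two conditions and √(1.5 × 0.5) = 0.866 for the vaccine mean minus Blood. The standard error is that SD × √(2/20).

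| Group contrast (unadjusted) | Effect | q = 0 | q = 0.5 | q = 1 |
|---|---|---|---|---|
| COVID-19 v influenza | 0.8(1 − q) | 69% | 23% | 5% |
| Vaccine mean v Blood | 0.8(1 + q)/2 | 30% | 57% | 81% |
| COVID-19 v Blood | 0.8 | 69% | 69% | 69% |

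The first two rows move in opposite directions with q, which is what makes the pair informative. The third row does not move, so it cannot discriminate. At q = 1 there is no COVID-19-specific effect, and 5% is the correct false-positive rate, not lost power.

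**4. Cost of sharing alpha.** Holm rejects any contrast with p ≤ 0.025, so power at that level is a floor. The same formulas at α = 0.025 give 58%, 15% and 2.5% for COVID-19 v influenza, and 20%, 45% and 72% for the vaccine mean v Blood.

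**5. Another effect size.** If the difference is scaled so that group × condition has the protocol's f = 0.25 at q = 0, it is 0.25/√((2/3)/3/4) = 1.06 SD. Omnibus power is then 94%, 85% and 94% at q = 0, 0.5 and 1, and COVID-19 v influenza has 91%, 37% and 5%. The symmetry does not depend on the assumed size.

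**The case against.** A reader might infer more: that selecting partly on a general scale makes influenza a contaminated reference level, dilutes the predicted COVID-19 difference, and rules out any COVID-19-specific conclusion. The document does not support this.

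- It never calls influenza a reference. Blood, COVID-19 and influenza are equal levels, Blood is a non-vaccine comparator, and the named control stimulus is the scrambled picture.
- The prediction is a group difference at COVID-19 imagery. A shared influenza response leaves that difference and COVID-19 v Blood untouched: 69% unadjusted at every q.
- A positive COVID-19 v influenza group contrast would be valid evidence of specificity, and a shared response only makes it harder to obtain. Including influenza is a strength.
- Section 2.1.1 still defines the hesitant group by reluctance toward the COVID-19 vaccine. Forming groups on the COVID-19 scale alone would not remove the link in the Introduction, which concerns hesitancy itself. How the scales are combined is detail that an article may leave to the full protocol.

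These points stand. It can also be said that the article makes no explicit claim of specificity, that its facial EMG prediction names no vaccine, and that q and the 0.8 SD are assumptions. That is fair and limits the point to the MEP analysis. It does not rescue the follow-up: section 2.8.1 assigns Tukey tests the task of finding condition-specific effects, and tests on cell means cannot separate these two patterns.

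**Conclusion.** The point holds as one about the follow-up analysis, not about recruitment or the choice of pictures. The omnibus test has equal power for a purely COVID-19 and a purely general vaccine effect (73% each under the assumed 0.8 SD, r = 0.5, 20 per group). The planned Tukey comparisons do not contain the group difference in COVID-19 minus influenza. Under the same assumptions, and with all 12 cells in the Tukey family, they leave about 19% power for the predicted group difference at COVID-19.

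The equality of omnibus power and the absence of the specificity contrast follow from the structure of the tests. The percentages rest on the assumed effect, on no group difference at Blood, and on an unknown q. The inference that the COVID-19 difference is diluted, or that specificity can never be claimed, should not be drawn. Specificity is unsupported only while the COVID-19 v influenza group contrast is untested or not significant. This is a change worth making before data are analysed; it is not a fault that invalidates the experiment.

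**What to change.** In section 2.8.1, replace the Tukey follow-up of the condition effect with two pre-stated 1-df group contrasts on the deltoid MEP:

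1. (COVID-19 + influenza)/2 v Blood, hesitant v accepting: a general vaccine effect.
2. COVID-19 v influenza, hesitant v accepting: a COVID-19-specific effect.

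Share α = 0.05 between them, for example by Holm, and state that COVID-19 specificity will be claimed only if the second is significant.

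Optionally, add one question on past influenza vaccination and report it descriptively; 20 hesitant participants will not support more. Regrouping on the COVID-19 scale alone is not needed.

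The cost is a few lines of text and a shared error rate. The second contrast is weak if much of the effect is shared: at a half share about 23% unadjusted, and at least 15% under Holm. A non-significant second contrast must therefore be reported as inconclusive on specificity, with its confidence interval, and not as proof of a general effect.

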## Abbreviations

The following abbreviations are used in this manuscript:

COVID-19	Coronavirus Disease 2019
VH	Vaccine Hesitancy
MEPs	Motor Evoked Potentials
EMG	Electromyography
SCR	Skin Conductance Response
WHO	World Health Organization
Vax	Vaccinated individuals
No-Vax	Non-Vaccinated individuals
TMS	Transcranial Magnetic Stimulation
IQ	Intelligence Quotient
OSP	Optimal Scalp Positions
ECR	Extensor Carpi Radialis
rMT	Resting Motor Threshold
μV	Microvolt
mV	Millivolt
Hz	Hertz
3D	Three Dimensional
VR	Virtual Reality
EDA	Electrodermal Activity
dB	Decibel
ANOVA	Analysis of Variance
CS+	Conditioned Stimulus Positive
CS-	Conditioned Stimulus Negative
Tukey’s HSD	Tukey’s Honestly Significant Difference

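### The control rule admits people on vaccination status alone, so a vaccinated but hesitant person fits both groups, and a matched comparison of existing attitude groups is labelled randomised.

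*Protocol article*

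**What the plan says.** The protocol article describes the grouping in several places.

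- **Basis of grouping (2.1.1, repeated in 2.2.1).** The 40 participants of each experiment "will be recruited for a randomized-controlled study and categorized based on their attitudes toward COVID-19 vaccination".
- **Hesitant group (2.1.1, 2.2.1), n = 20.** "Individuals reluctant to receive the COVID-19 vaccine, identified using validated psychometric tools". Being unvaccinated is not a condition.
- **Control group (2.1.1, 2.2.1), n = 20.** "Individuals who are vaccinated or express no hesitation toward vaccination".
- **Intended contrast (Introduction, second aim).** "testing whether hesitant individuals exhibit altered fear acquisition, extinction patterns compared to non-hesitant controls". The Introduction also describes hesitancy as "defined as delay or refusal to accept the vaccine".
- **Analysis factor (2.1.2, 2.2.2, 2.8).** Group is Vax versus No-Vax. The Abbreviations spell out Vax by vaccination and No-Vax as "Non-Vaccinated individuals".
- **Comparability (2.1.1, 2.2.1).** "To ensure comparability, groups will be matched by demographic variables, including age, gender, and educational level".
- **What is randomised.** Stimulus order in Experiment 1 (2.7.1: "To ensure a balanced and unbiased presentation, stimuli will be randomly presented"), the timing of the TMS pulse (2.6.1, 2.7.1) and the order of the doors at habituation in Experiment 2 (2.7.2). No random allocation of participants is described.

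**The concern.** There are two faults in what the article states.

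First, the two group rules use different variables. One is an attitude measured on scales. The other is satisfied by an attitude or by a past act. People can be vaccinated and still hesitant, and the article's own definition of hesitancy includes delay, which ends in vaccination for some. Such a person fits both rules. A recruiter who follows the control rule literally can enter them as a control, which conflicts with the aim of comparing hesitant with non-hesitant people. Group is the between-subjects factor in every planned ANOVA in 2.8, and associations with hesitancy are to be read from between-group comparisons, so hesitant people among the controls would shrink those contrasts.

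Second, the randomised-controlled label describes a property the design does not have. Matching on age, gender and education balances those variables at best. It does not protect the group comparison from other differences between people who hold different attitudes.

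**Working it through.** **Step 1: the rules side by side.** Classify the four possible kinds of participant by each definition.

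| Person | Hesitant rule (2.1.1, 2.2.1) | Control rule (2.1.1, 2.2.1) | Label in Abbreviations |
|---|---|---|---|
| Unvaccinated, hesitant | yes | no | No-Vax |
| Vaccinated, not hesitant | no | yes | Vax |
| Vaccinated, hesitant | yes | yes | Vax |
| Unvaccinated, not hesitant | no | yes | No-Vax |

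The third row meets both rules. In the fourth row the person is a control by the participant rules but No-Vax by the abbreviation. The definitions agree only in the first two rows.

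**Step 2: the plan's own sample size.** Inputs from 2.1.2 and 2.2.2: k = 2 groups, m = 6 repeated measures, f = 0.25, r = 0.5, sphericity 1, alpha 0.05, power 0.95. For a within-between interaction:

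- noncentrality λ = f² × N × m / (1 − r)
- df1 = (k − 1)(m − 1), df2 = (N − k)(m − 1)

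At N = 40, λ = 0.0625 × 40 × 6 / 0.5 = 30, with 5 and 190 degrees of freedom, and power is 0.995. These inputs reach 0.95 at N = 28 (power 0.954), so the stated 40 is not reproduced. It is returned exactly if four groups are entered (power 0.952). That discrepancy is a separate matter, and the present point does not depend on it.

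**Step 3: effect of hesitant people among the controls.** Let q be the share of controls who are hesitant and respond like the hesitant group. The control mean moves a fraction q of the way to the hesitant mean, so each group contrast is multiplied by (1 − q), and f becomes 0.25 × (1 − q). The documents give no value for q; 10, 20 and 30% (2, 4 and 6 of 20 controls) are assumptions. Any added spread within the mixed control group is ignored.

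Two tests are shown at N = 40: the six-measure interaction used for the sample size, and a group-by-condition test on three measures (df 2 and 76).

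| q | f(1 − q) | λ, m = 6 | Power, m = 6 | λ, m = 3 | Power, m = 3 |
|---|---|---|---|---|---|
| 0 | 0.250 | 30.0 | 0.995 | 15.0 | 0.935 |
| 10% | 0.225 | 24.3 | 0.979 | 12.15 | 0.874 |
| 20% | 0.200 | 19.2 | 0.936 | 9.6 | 0.782 |
| 30% | 0.175 | 14.7 | 0.847 | 7.35 | 0.660 |

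For the six-measure test, the N needed for 95% power goes from 28 to 34, 44 and 56. Power at N = 40 therefore drops below the planned 0.95 somewhere between 2 and 4 hesitant controls out of 20, on the more favourable of the two tests.

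**Step 4: the design label.** The sentence that calls each study randomised-controlled is the same one that sorts participants by existing attitude. Everything the article randomises is a feature of presentation or timing within a participant. None of it bears on who is in which group.

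**The case against.** The best defence is that attitude is the declared basis of grouping, the control arm is named vaccine-accepting, and the Introduction speaks of non-hesitant controls. Read that way, the scales take precedence, a vaccinated person with a hesitant score goes to the hesitant group, and nothing is diluted. The hesitant rule can also be read as covering only people who have not yet taken the vaccine, which narrows the overlap. This stands to the extent that dilution is a possibility and not a demonstrated fact. It does not remove the fault, because no precedence is stated and the control rule makes vaccination sufficient.

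Several stronger readings are tempting but not supported:

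- **That the contrast is diluted as planned.** This depends on how overlapping people are placed, which the text leaves open.
- **That anyone vaccinated late scores as hesitant.** The scales are not shown, and the general definition in the Introduction does not say how past delay maps to a current score.
- **That the abbreviations are a further assignment rule.** They are a glossary. The mismatch needs correcting, but sections 2.1.1 and 2.2.1 decide who enters each group.
- **That every analysis is affected.** The correlations and hierarchical regressions at the end of 2.8.2 state no group factor.
- **That power is roughly halved.** Such figures need a large-effect two-sample t-test that is not the planned analysis. The group main effect does have low power at N = 40 (0.523), but that is with no misclassification at all.
- **That the article draws causal conclusions.** The aims raise the possibility that fear learning underlies hesitancy, but the same aim, section 2.8.2 and the Discussion also use the language of association.

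Numeric cut-offs for the scales may sit in a fuller document, and their absence is not part of this point.

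**Conclusion.** The point holds as two errors of statement. The control rule, as written, overlaps with the hesitant rule and conflicts with the intended contrast and with the factor's labels. The randomised-controlled description is wrong for both experiments. Both stand whatever the share of overlapping people.

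The statistical cost is conditional. Under the dilution model in the working, an assumed 10 to 30% of hesitant controls costs about 2 to 15 percentage points of power on the six-measure interaction (0.995 to between 0.979 and 0.847) and about 6 to 28 points on the three-measure test (0.935 to between 0.874 and 0.660). It is zero if the scales are applied to everyone and take precedence. This should be fixed, preferably before enrolment, since group assignment is hard to repair afterwards. It does not by itself invalidate the planned analyses.

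**What to change.** 1. In 2.1.1 and 2.2.1, remove the vaccination-status alternative from the control rule. Assign both groups on the hesitancy scales already named there, with mutually exclusive categories.
2. Record vaccination status as a descriptor only.
3. Define the Vax/No-Vax factor as accepting/hesitant in 2.1.2, 2.2.2, 2.8 and the Abbreviations.
4. In both participant sections, replace the randomised-controlled description with observational matched-group study. Say, if wished, that stimulus order and pulse timing are randomised. Keep group conclusions to associations.

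The cost is small: changes of wording and a screening rule based on scales already in use, with no new measurement and no change to any stated figure. Vaccinated people with hesitant scores no longer qualify as controls, which may make recruiting that group a little slower.
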